### Sample size

A total of 16 pediatric ICUs, including 100 participants per location, for a
total of 1,600 participants will be selected to detect a decrease of 2.3 days of
hospitalization in the intervention units compared to the control unit. To
consider the standard deviation (SD), the data from the TeleICU project
indicators were used for a SD of 6.2 days in the control units and 7.1 in the
intervention group, in addition to an intraclass correlation coefficient of
0.05, power of 80% and alpha of 5%. WinPepi software, version 11.65, was chosen
to determine the sample size calculation.

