### Eligibility of participants

The eligibility criteria for the participants are patients admitted to the
selected pediatric ICUs ≥ 29 days and < 18 years of age, with a stay
of more than 24 hours and, in case of death, with a stay of more than 8
hours.

The exclusion criteria are patients with incomplete medical records or missing
data, with a stay > 90 days in the ICU, who are in the intervention cluster
and did not receive telemedicine care, and those whose guardians did not agree
to participate in the study and/or did not sign the informed consent.

The recruitment of study units and study participants will follow the criteria of
the 2010 statement of the Consolidated Standards of Reporting Trials (CONSORT)
for cluster randomized trials and is detailed in figure 1.

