### Outcomes

The primary outcome measure will be the length of stay of the patients in the
PICU, defined as the difference between the date of discharge and the date of
admission to the ICU. The secondary outcomes will be mortality rate, IMV-free
days, days using antibiotics, days using vasoactive drugs and days using
sedoanalgesia.

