### Statistical analysis

Statistical analyses will be performed both by intention-to-treat and by
protocol, considering that the study design is a cluster RCT, and data from the
observed pediatric ICUs will be analyzed.

The description of the information regarding the PICUs and the characteristics of
the participants will be presented for the control and intervention groups, in
which the categorical variables will be presented by absolute and relative
frequency, while the continuous variables will be first evaluated for normality
by means of visual verification of histogram and Shapiro‒Wilk test and presented
as the mean and SD or median and interquartile range (IQR), depending on the
data distribution, as shown in table 1S (Supplementary Material).

For the primary outcome of the study, a noninferiority analysis will be performed
through modeling, considering that the data are correlated in each ICU, by
generalized mixed models adjusted for variables of interest to the researchers.
Regarding the secondary outcomes, correlated data models will also be used;
however, the probability distribution of each outcome will be taken into
account. Table 2S (Supplementary Material) describes the data to be
analyzed.

Sensitivity analyses will be conducted only for the primary outcome in the
intervention group to verify whether adherence to teleround can impact the
length of stay.

We will also analyze some exploratory results regarding the days of IMV use,
number of days off for each ventilatory support and days off the use of
medications such as antibiotics, sedoanalgesia, antifungal and antiviral, water
balance during hospitalization and verification of permanence in hospital
intensive care (use of IMV or sedoanalgesia) in participants who spent at least
8 days in the pediatric ICU, as shown in table 3S (Supplementary Material).

All statistical analyses will be performed considering a significance level of
0.05. The software to perform all the analyses will be the R program, version
4.2.1 or a later version.

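### Excluding PICU stays over 90 days cuts on the primary outcome after randomisation and conflicts with the intention-to-treat analysis; the size of any bias is unknown and may be negligible

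*Protocol article*

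**What the plan says.** Three sections of the Protocol article bear on this.

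- **Eligibility of participants.** Among the exclusions are patients "with a stay > 90 days in the ICU". The rule applies to both arms. The same sentence also removes patients with incomplete records or missing data, and those "who are in the intervention cluster" but had no telemedicine.
- **Outcomes.** "The primary outcome measure will be the length of stay of the patients in the" PICU, counted as discharge date minus admission date.
- **Statistical analysis.** "Statistical analyses will be performed both by intention-to-treat and by" protocol. The only sensitivity analysis described concerns teleround adherence within the intervention group.

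The section on missing data rules out imputation of outcomes. No section returns stays over 90 days to the intention-to-treat set, caps or censors them, or plans an analysis that includes them.

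**The concern.** An eligibility criterion should be knowable at or near entry. Whether a stay passes 90 days is known only after 90 days of the care that was allocated to the unit. The rule therefore selects patients on the dependent variable, after randomisation.

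The trial expects the intervention to change that variable: the Sample size section plans "to detect a decrease of 2.3 days of" hospitalisation. If the change reaches the longest stays, it changes who crosses the line. A child whose stay falls from 100 to 80 days is counted in the intervention arm at 80, while a comparable control child at 100 is removed. If telemedicine instead lengthened some of the longest stays, those children would leave the intervention arm and the harm would not show. Attenuation towards no difference deserves extra care here, because the Statistical analysis section calls the primary analysis one of noninferiority.

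The excluded children also leave every secondary outcome, mortality included.

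**Working it through.** **1. The plan's own figure.** Inputs from the Sample size section: difference 2.3 days, SDs 6.2 and 7.1, ICC 0.05, 100 children per unit, power 80%, alpha 5% (taken as two-sided).

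- Per arm without clustering: (1.960 + 0.842)² × (6.2² + 7.1²) / 2.3² = 131.8
- Design effect: 1 + 99 × 0.05 = 5.95
- Per arm with clustering: 131.8 × 5.95 = 784.4, or 7.84 units, rounded up to 8
- Total: 16 units and 1,600 children, as stated

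The sample size reproduces, and this point does not question it.

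**2. No effect on stay.** If both arms have the same stay distribution, the cut removes the same expected share from each and creates no difference.

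**3. Planning SDs.** The article gives no mean stay, so I assume lognormal stays with control means of 8, 11 and 14 days, an intervention mean 2.3 days lower, and SDs 6.2 and 7.1.

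| Control mean | Expected exclusions per 800, control | Intervention | Difference after exclusion |
|---|---|---|---|
| 8 | 0.04 | 0.34 | 2.34 |
| 11 | 0.01 | 0.11 | 2.31 |
| 14 | 0.002 | 0.03 | 2.30 |

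Fewer than one child per arm is expected to be removed, and the effect is negligible. The difference rises slightly here because the larger intervention SD puts more of that arm in the tail.

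**4. Heavier tails.** Assumptions: lognormal stays, control median 6, 8 or 11 days, log-SD s = 0.8 or 1.0, and the intervention median multiplied by 1 − 2.3/11 = 0.791 (a 21% shortening). The 11 is borrowed from the stratification cut on unit median stay, the only location figure in the article. With mu = ln(median) and Φ the normal distribution function:

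- Share above 90: P = 1 − Φ((ln 90 − mu)/s)
- Mean with stays over 90 removed: exp(mu + s²/2) × Φ((ln 90 − mu − s²)/s) / (1 − P)
- Mean of min(stay, 90): exp(mu + s²/2) × Φ((ln 90 − mu − s²)/s) + 90P

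Example, median 8 and s = 1.0: the control mean is 13.19 in full, 12.26 with exclusion and 12.86 capped. The intervention mean is 10.43, 9.96 and 10.28. The differences are 2.76, 2.30 and 2.58.

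| Median, s | Control above 90 | Full difference | Excluded (kept) | Capped (kept) |
|---|---|---|---|---|
| 6, 0.8 | 0.04% | 1.73 | 1.70 (99%) | 1.72 (99.7%) |
| 6, 1.0 | 0.34% | 2.07 | 1.86 (90%) | 2.00 (96%) |
| 8, 0.8 | 0.12% | 2.30 | 2.22 (96%) | 2.28 (99%) |
| 8, 1.0 | 0.78% | 2.76 | 2.30 (83%) | 2.58 (94%) |
| 11, 0.8 | 0.43% | 3.17 | 2.90 (92%) | 3.09 (97%) |
| 11, 1.0 | 1.78% | 3.79 | 2.80 (74%) | 3.36 (89%) |

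The percentages kept come from unrounded differences. In the intervention arm, 0.01% to 0.97% exceed 90 days.

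**5. Cost of retaining them.** At median 8 and s = 1.0, the control SD is 12.9 with exclusion and 14.5 with capping. The difference divided by that SD is 0.179 and 0.178, so precision is practically unchanged.

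**The case against.** The best defence is that the rule is the same in both arms and may almost never apply. The Sample size section says that project "indicators were used for a SD of 6.2 days in the control units and 7.1 in the" intervention group, and with such SDs fewer than one child per arm is expected past 90 days. The heavier-tailed cases sit uneasily with those figures: even after removal of stays over 90 days, their control SDs run from 7.6 to 15.4. This stands as a limit on size. It does not settle the matter, because the article does not say whether those SDs came from data with the same cut.

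A reader might infer more than the documents support, in three ways.

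- *That the longest stays are certain to be lost unequally by arm.* The text does not show this. In expectation it follows only if telemedicine, or discharge and transfer decisions near day 90 in an open-label trial, alters the upper tail.
- *That a true benefit would be turned into apparent harm.* In every case computed, the intervention mean remains lower. The result is attenuation, not reversal.
- *That this rule alone defeats intention-to-treat.* The same sentence removes untreated children from the intervention arm only, and children with missing data. The one-arm exclusion is the more direct breach.

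It could also be said that the promised intention-to-treat analysis silently overrides the exclusion. The article lists it as a general exclusion, does not tie it to the per-protocol set, and nowhere readmits these children.

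**Conclusion.** The point holds as a fault in the stated rule. The article excludes on a value of the primary outcome that is known only after randomisation, and this cannot be reconciled with its intention-to-treat analysis. That conclusion needs no assumption.

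The size of the bias does, since neither a mean stay nor a share above 90 days is given. It is negligible under the planning SDs. Under the lognormal assumptions above, the estimated difference keeps 74-99% of its true value. A tail heavier than assumed would lose more, and an intervention with no effect on the tail would lose nothing. If long stays are rare, the exclusion gains nothing. If they are not rare, it can distort the primary estimate.

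**What to change.** Delete the over-90-day criterion from the exclusions. For the intention-to-treat analysis:

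- Keep every otherwise eligible enrolled child in the arm of the unit.
- Handle stay identically in both arms: as observed, or as min(stay, 90) if follow-up ends at day 90. State which. Capping makes the target a stay restricted to 90 days.
- Keep these children in the secondary outcomes over the same window.
- Report the number above 90 days by arm.
- Move the 90-day cut to a sensitivity analysis.

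This takes a line or two in each of the eligibility and analysis sections and needs no extra patients. The outcome SD grows slightly (12.9 to 14.5 in the worked case, when capped). If uncapped stays are used, data collection must continue past day 90 for a few children.

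This change alone does not restore intention-to-treat. The exclusions for missing data and for intervention-unit children without telemedicine are separate departures and must be dealt with as well.

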## METHODS

### Study design

The present protocol refers to a study designed as an RCT, by cluster, open
label, in pediatric ICUs, with an allocation ratio of 1:1, in which the
hospitals are the clusters, to perform the comparison of the group intervention
(support of Telemedicine for patients admitted to the pediatric ICU) with a
control group (usual care in the pediatric ICU).

The RCT was registered in the Brazilian Registry of Clinical Trials (ReBEC) on
March 22, 2022, and the present protocol provides additional details on the
study design and methodology, based on the CONSORT 2010 Statement.^(26-28)^

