### Intervention (Telemedicine)

The intervention group, during the data collection period, will receive
telerounds from Monday to Friday and will have specialists available on demand
(as cases and specific needs arise, the pediatric ICUs may request evaluation by
specialists from the proposing institution) and continuing education activities.
The telerounds will be case discussions with pediatric intensivists at a
distance and doctors of other specialties on demand for the debate on conduct
based on the best scientific evidence. The intensivists of the project will
connect through a telemedicine CART (Figure 1S - Supplementary Material) with
the pediatric ICU team of the participating centers daily, from Monday to
Friday, to perform medical consultations at the bedside to establish diagnoses,
guide the therapeutic conduct and perform clinical follow-up.

The intensivist of the project will record the appointments on a digital
platform, especially designed for the activity. A treatment plan will be
suggested by the project team (clinical management recommendations). The
physician of the participating center will be free to decide whether to accept
the recommendations. These recommendations will be reassessed 24 hours later in
the next teleround. The proposal is to maintain horizontal care, in which the
patient is monitored from the first day of hospitalization until discharge.

Concurrently with the period of application of the intervention, continuing
education activities will be made available to all professionals of the
participating centers’ teams. Education activities will be held monthly and will
consist of video classes, discussions of complex cases and DE courses. The video
classes will be made available synchronously and asynchronously, with topics
chosen according to the needs of each center. The discussions of complex cases
will be meetings in which each participating center will be responsible for
choosing a case considered a challenge to the team, and medical specialists will
be invited to participate in the discussions. The DE courses will be developed
by the proposing institution and will be available on a platform specific to the
study, with specific themes to qualify care in pediatric intensive care. These
courses may be attended at any time by staff of the participating centers.

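### A one-arm exclusion of untreated intervention-cluster children contradicts the promised intention-to-treat analysis and selects on length of stay and early death

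*Protocol article*

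**What the plan says.** All references are to the protocol article.

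- **Study design:** the "hospitals are the clusters", allocated 1:1.
- **Eligibility of participants:** survivors qualify after more than 24 hours; deaths qualify "in case of death, with a stay of more than 8" hours. The exclusion list includes patients "who are in the intervention cluster" "and did not receive telemedicine care". Nothing comparable is listed for control clusters.
- **Intervention (Telemedicine):** intervention units receive "telerounds from Monday to Friday and will have specialists available on demand". No weekend rounds are described.
- **Outcomes:** "The primary outcome measure will be the length of stay of the patients in the" PICU. "The secondary outcomes will be mortality rate", followed by several duration measures.
- **Statistical analysis:** "Statistical analyses will be performed both by intention-to-treat and by" protocol. Nothing there returns the excluded children to the intention-to-treat set.

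**The concern.** Clusters are randomised, so the two arms are comparable only if the same kinds of children are counted in each. Here a child in an intervention unit must have received the intervention to be counted, while a child in a control unit need only be eligible. Because the rule sits among the study exclusions rather than in a per-protocol definition, the intention-to-treat set as written contains only treated children in one arm and all eligible children in the other.

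The selection is also related to the outcomes. To be seen at a weekday round, a child must stay, and survive, until one takes place. Dropping short stays from the intervention arm alone raises its mean stay and can mask a real reduction. Dropping early deaths from that arm alone lowers its mortality, provided deaths are removed at a higher rate than survivors. A larger sample corrects neither.

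**Working it through.** **1. The plan's own sample size.** Inputs from Sample size: difference 2.3 days, SDs 6.2 and 7.1, ICC 0.05, 100 children per unit, power 80%, alpha 5% (taken as two-sided).

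- Per arm before clustering: (6.2² + 7.1²)(1.96 + 0.84)² / 2.3² ≈ 131.8
- Design effect: 1 + 99 × 0.05 = 5.95
- Per arm after clustering: 131.8 × 5.95 ≈ 784, or 7.84 units, rounded up to 8
- Total: 16 units and 1,600 children, as stated

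The section states no allowance for excluded or untreated children.

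**2. Chance of meeting no teleround.** Assume one round at a fixed hour each weekday and admissions uniform over the week. Each week then has four gaps of 1 day and one of 3 days (Friday to Monday). A stay of L days misses every round if it fits inside one gap:

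- 1 ≤ L ≤ 3: (3 − L)/7, which is 2/7 = 29% at 1 day, 1/7 = 14% at 2 days and 0 at 3 days
- L < 1: [4(1 − L) + (3 − L)]/7 = 1 − 5L/7, which is 76% at 8 hours and falls to 29% at 24 hours

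The under-1-day range concerns deaths only, because survivors need more than 24 hours.

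**3. Effect on the arm means, by simulation with no true effect.** Further assumptions, none from the documents except the SD: survivor stays gamma or lognormal beyond 24 hours, nominal mean 6, 8 or 11 days, SD 6.2; 5% mortality; mean time to death 3 days after hour 8; each round missed independently with the probability shown. Ranges run over the two distributions and three means.

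| Rounds missed | Intervention children excluded | Shift in mean stay (days) | Intervention deaths removed | Apparent mortality (true 5.0%) |
|---|---|---|---|---|
| 0% | 0.9–8.0% | +0.08 to +0.39 | 16–17% | 4.2–4.6% |
| 20% | 1.5–13.0% | +0.13 to +0.64 | 23–24% | 3.9–4.4% |
| 40% | 3.0–20.4% | +0.23 to +1.03 | 32% | 3.5–4.3% |

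The top of each stay range is the gamma case with mean 6 days. A separate grid with mean stays of 7 to 12 days and SDs of 6 to 11 gave 0 to +0.26 day with all rounds delivered, and up to about +1.1 days with only 50–80% delivered.

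**4. What a shift does to power.** The standard error is √[(6.2² + 7.1²)/(800/5.95)] = √(88.85/134.5) ≈ 0.813 day, so power at 2.3 days is Φ(2.3/0.813 − 1.96) ≈ 81%. Holding the variance fixed:

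- shift of 0.1 day, apparent effect 2.2: about 77%
- shift of 0.3 day, apparent effect 2.0: about 69%
- shift of 1.0 day, apparent effect 1.3: about 36%

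**The case against.** The asymmetry is not in dispute. The case on the other side concerns how far it can be pushed.

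**A reader might infer that the excluded children's data are never collected, so that intention-to-treat is impossible.** The article does not say this. It promises both analyses and has monitors follow teleround adherence, so the criterion may be a per-protocol rule misplaced in a condensed article. Figure 1 and the full protocol could not be consulted. What stands is that the two sections conflict as written.

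**A reader might infer that about half of the 2.3-day target is lost.** That needs roughly half the rounds to be missed (40% in the shortest-stay scenario), and the documents give no delivery rate. Stays may also be long: randomisation is stratified at a unit median of 11 days. With mean stays of 11 to 12.5 days and the plan's SDs, the shift is at most about +0.05 day at full delivery and +0.37 day at 50% delivery. With a 7-day mean and SD 6.2 it is +0.15 to +0.21 and +0.73 to +0.87 day. Full delivery is not assured either: the Discussion acknowledges dependence on the internet, and an adherence sensitivity analysis is planned.

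**A reader might infer an established false survival benefit.** The mortality figures rest on assumed risk and timing of death, and the share of deaths at 8 to 24 hours is unknown. Mortality is also secondary; on the primary outcome the bias can hide a benefit but not create one.

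**On-demand specialist contact might count as telemedicine care.** That would reduce the exclusions. It would not make the rule symmetric.

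**Conclusion.** The point stands as a contradiction between Eligibility of participants and Statistical analysis. A post-randomisation exclusion based on treatment received, in one arm only, is incompatible with intention-to-treat, and nothing in the article resolves it.

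The direction for length of stay is clear: against telemedicine. For mortality it favours telemedicine in every scenario tried, including full delivery, given the assumed timing of deaths.

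The size is unknown. With a fixed-hour weekday round and uniform admissions, the stay bias is about 0 to +0.3 day when all rounds take place, slightly more if mean stay is near 6 days. A figure near +1 day belongs to short stays with roughly half the rounds missed and should not be presented as the expected loss. The correction should precede data collection as far as possible, because children who are not enrolled cannot be recovered at analysis.

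**What to change.** 1. Remove non-receipt of telemedicine from the study exclusion criteria.
2. Enrol, collect and analyse every otherwise eligible, consenting child in all 16 units by the unit's allocation, and name this intention-to-treat analysis as primary.
3. Use receipt of telemedicine only to define the secondary per-protocol set, and state what counts as receipt (a teleround alone, or also on-demand specialist contact). Being in the unit at a scheduled round hour is not the same as receiving a round and should not stand in for it.
4. State that the per-protocol comparison is non-randomised, because receipt depends on length of stay.

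The other exclusions applied after admission (missing data, stays over 90 days) are worded for both arms and remain, so this change removes the one-sided selection but not every departure from a full intention-to-treat set.

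Cost: a wording change; consent and data collection for short stayers and early deaths who would otherwise be dropped; and slight dilution of the effect by untreated children. The planned 1,600 is unchanged.

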**Figure 1 f1:**
[figure not shown]
Recruitment of study units and participants.

### Data collection

#### Software for data collection

The data will be collected and managed using Research Electronic Data Capture
(REDCap®), an electronic tool for capturing, storing and managing
data.^(32,33)^ The variables of interest
that will be collected are sociodemographic data, such as date of birth,
sex, self-reported race and age (calculated from the date of birth) and
clinical data, described in chart 1S (Supplementary Material).

#### Training for data collection

Both the intervention and control groups will receive training, in which
theoretical and practical contents for the collection and management of
clinical data will be addressed through REDCap®. In addition, for the
intervention group, training will be offered to the health care team that
will include content regarding the use of the digital platform to record the
attendance and protocol for the telerounds.

